#### Sample size justification

On repeated measures ANOVA, 60 study completers will allow us to observe an effect size of 0.34 at two-tailed alpha = 0.05 and Power (1-Beta) =0.8 [38]. In our previous cross-sectional findings in chronic lithium users, the effect size of statins on NDI was 0.33 [21], however that was not an intervention study. We acknowledge that there is relatively little data at the current time to justify the sample size. This RCT will provide the necessary and adequate data to plan a subsequent larger RCT [39].

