**Methods:**

We will conduct a 12-week, double-blind placebo-controlled RCT of atorvastatin for lithium-induced NDI at McGill University, Montreal, Canada. We will recruit 60 current lithium users, aged 18–85, who have indicators of NDI, which we defined as urine osmolality (UOsm) < 600 mOsm/kg after 10-h fluid restriction. We will randomize patients to atorvastatin (20 mg/day) or placebo for 12 weeks. We will examine whether this improves measures of NDI: UOsm and aquaporin (AQP2) excretion at 12-week follow-up, adjusted for baseline.

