## Methods

### Study design and study sample

This is a double-blind, placebo-controlled RCT examining the effectiveness of atorvastatin versus placebo in the treatment of lithium-induced NDI. The study will take place at three tertiary care mental health sites in Montreal, Canada: Douglas Mental Health University Institute (DMHUI), Jewish General Hospital (JGH) and McGill University Health Centre (MUHC).

The study will involve treatment with atorvastatin (20 mg/day) or placebo over a period of 12 weeks. We are aiming to recruit sixty individuals between the ages of 18 and 85 with any psychiatric diagnosis who are currently taking lithium for at least 2 months and have a urine osmolality < 600 mOsm/kg after 10-h water restriction. We opted for a urinary osmolality of < 600 mOsm/Kg: patients with < 600 mOsm/kg are at risk of future NDI-related complications, such as CKD and they constitute a large percentage of lithium users (50% of patients). Other studies have used similar, if not less conservative definitions for NDI [25], which are nonetheless of clinical importance and utility [15]. Other authors have used similar or more liberal definitions in NDI treatment studies [25].

The full inclusion and exclusion criteria can be found in Table 1.

**Table 1 Tab1:** Inclusion and exclusion criteria

Inclusion Criteria	Exclusion Criteria
Between ages 18–85	Already taking statins (at least 6 weeks prior to screening)
Bipolar Diagnosis in any phase of illness: euthymic, depressed or hypomanic. Any schizoaffective diagnosis.	History of adverse reaction to statins; allergy to statins
Diagnosed with NDI, defined by routine 10 h water restriction urine osmolality < 600 mOsm/Kg	Contraindications to statin use: pregnancy or lactation, use of fibrates and heavy alcohol use
Currently taking lithium medication (at least 2 months)	Inability to give consent or deemed to have moderate-severe cognitive disturbances by treating clinician
Able and willing to give informed consent	Active liver disease
	Baseline LDL level < 1.5

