### Overview of study procedures

In this double-blind RCT, sixty patients will receive 12 weeks of either treatment (20 mg/day atorvastatin) or placebo. The study will require three visits at baseline, 4-week and 12-week follow-up, for which participants will be compensated. During each visit, blood and urine samples after 10 h of water restriction and 12 h of fasting will be requested. In addition to the primary and secondary outcomes, patients will be monitored for safety using blood tests for liver function (AST and ALT), cholesterol (e.g. low-density lipoprotein (LDL)) and lithium toxicity (lithium levels, estimated glomerular filtration rate (eGFR)). Patients will also complete questionnaires about their medical history and mental health. Mood assessments for depression and mania symptoms will be completed at baseline, 4-week and 12-week follow-up, including the Montgomery-Asberg Depression Rating Scale (MADRS) [26], Young Mania Rating Scale (YMRS) [27], and the Quick Inventory of Depressive Symptoms, Self-report-16 (QIDS-16) [28], Altman Self-Rating Mania Scale (ASMRS) [29].

The primary outcome is change in 10 h water restriction urine osmolality (mOsm/kg) and will be assessed at baseline, 4-week and 12-week follow-up visits (Table 2).

**Table 2 Tab2:** Baseline and follow-up visits schedule of events and assessments

Assessment	Screen	Baseline	4-week	12-week
Blood	√	√	√	√
Urine osmolality	√	√	√	√
Medical History	√	√		√
Mood Assessment		√	√	√
1.MADRS		√	√	√
2.YMRS		√	√	√
3. QIDS		√	√	√
4. Altman self-rating mania scale		√	√	√

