## Discussion

This paper described the methodology of a clinical trial to assess the effectiveness of atorvastatin in treating NDI in lithium users. If atorvastatin is ultimately found to be effective for NDI, some of the risk associated to CKD, hypernatremia and AKI attributable to lithium could be attenuated, allowing a greater number of persons to use lithium more safely. Minimizing these risks of kidney disease associated with lithium use is important because it could potentially prevent acute and chronic medical health care services related to renal disease and psychiatric illness, possibly saving significant personal and health care costs worldwide.

The present study is the first RCT of atorvastatin in the treatment of Li-induced NDI. This study represents an advance in methodological rigor compared to previous studies examining the treatment of NDI [17]. These studies were similar in design to the present study, however these used very small sample sizes (*n* = 9, *n* = 11) [18, 25]. Hydrochlorothiazide (HCTZ), other diuretics, non-steroidal anti-inflammatory drugs (NSAIDs), and aspirin (ASA) have also been tried in NDI, but the studies supporting their use are almost exclusively from small uncontrolled trials/chart reviews [17]. In addition, there are limitations to the use of amiloride, diuretics, NSAIDs and other medications previously tested to treat NDI: these medications can lead to elevations in lithium levels contributing to increased risk of lithium-associated CNS and acute renal toxicity. We present an RCT with comparatively large sample size (*n* = 60), which will provide preliminary data to guide larger-scale international collaborative study.

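### The 80% power is stated for 60 completers, but only 60 patients are to be recruited, so the figure makes no allowance for loss over 12 weeks

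*Protocol article*

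**What the plan says.** Under Sample size justification, the protocol article bases its power on repeated measures ANOVA: "60 study completers will allow us to observe an effect size of 0.34", "at two-tailed alpha = 0.05 and Power (1-Beta) =0.8". The unit counted there is the patient who completes.

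Elsewhere the same number counts patients at entry:

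- Abstract, Methods: "We will recruit 60 current lithium users, aged 18–85, who have indicators of NDI".
- Study design and study sample: "We are aiming to recruit sixty individuals between the ages of 18 and 85".
- Overview of study procedures: "sixty patients will receive 12 weeks of either treatment (20 mg/day atorvastatin) or placebo".
- Discussion: "We present an RCT with comparatively large sample size", followed by n = 60 in brackets.

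The article gives no expected loss, inflation, replacement rule or recruitment target above 60. Under Planned analysis, the primary comparison is urine osmolality at 12 weeks between the two arms, adjusted for baseline. Allocation is 1:1 (Randomization and concealment).

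**The concern.** Recruited, treated and completing are three different counts. By choosing the word completers, the sample size paragraph separates the last from the first two, yet the article sets all three at 60. They coincide only if every randomised patient is followed to 12 weeks and gives a usable sample.

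At stake is how the result is read. The same paragraph presents the trial as an adequate basis for planning a larger one. If some patients are lost and the result is null, a reader who takes the printed 80% at face value may credit the trial with more power than its stated basis supports.

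**Working it through.** **Inputs from the article:** effect size 0.34, two-sided alpha 0.05, power 0.80, 60 completers, two arms at 1:1, repeated measures ANOVA.

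**Inputs not given, hence assumed:** the effect-size scale (taken as Cohen's f), the number of measurements m, the within-patient correlation rho, and the loss rate (10%, 15% and 20% for illustration).

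**Step 1. Can the stated 80% be reproduced?** For the between-group effect with two arms, power is the upper tail of a noncentral F with 1 and N − 2 degrees of freedom and

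lambda = f² × N × m / (1 + (m − 1) × rho).

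With f = 0.34 (f² = 0.1156) and N = 60:

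| m | rho | lambda | power |
|---|---|---|---|
| 2 | 0.7 | 13.872 / 1.7 = 8.16 | 80.2% |
| 3 | 0.8 | 20.808 / 2.6 = 8.00 | 79.4% |
| 2 | 0.5 | 13.872 / 1.5 = 9.25 | 84.9% |
| 3 | 0.5 | 20.808 / 2.0 = 10.40 | 88.7% |

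The figure is attainable, at rho of about 0.71 (m = 2) or 0.78 (m = 3). It is not uniquely reproducible, because rho and m are not stated.

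**Step 2. Effect of loss, taking 80% at 60 completers as stated.** Calibrated that way, lambda is 8.117 at N = 60 and scales with N, whichever m is used.

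| Assumed loss | Completers | lambda | Power for 0.34 | Detectable effect at 80% |
|---|---|---|---|---|
| 0% | 60 | 8.117 | 80.0% | 0.340 |
| 10% | 60 × 0.90 = 54 | 7.305 | 75.6% | 0.359 |
| 15% | 60 × 0.85 = 51 | 6.899 | 73.1% | 0.370 |
| 20% | 60 × 0.80 = 48 | 6.494 | 70.4% | 0.382 |

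A normal approximation, Φ((1.96 + 0.84) × √(1 − loss) − 1.96), gives 75.7%, 73.3% and 70.7%. Small losses matter little: one patient gives about 79.3% and three give about 77.9%.

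**Step 3. Sensitivity to the unstated correlation.** With f = 0.34 and rho = 0.5:

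- m = 2: lambda at 54 completers is 0.1156 × 54 × 2 / 1.5 = 8.32, power 80.8%. At 51 it is 78.5% and at 48 it is 75.9%.
- m = 3: lambda at 48 completers is 0.1156 × 48 × 3 / 2 = 8.32, power 80.6%.

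Under those inputs 60 randomised patients would carry some slack. At rho of about 0.7 to 0.8, the range that reproduces the stated 80%, there is none.

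**Step 4. The planned comparison.** If 0.34 is f, then for two equal arms d = 2 × 0.34 = 0.68. A baseline-adjusted 12-week comparison with baseline correlation r has noncentrality d / √(1 − r²) × √(N / 4). At an assumed r = 0.5, power is 84.9%, 80.8%, 78.5% and 75.9% at 60, 54, 51 and 48 completers. So on this reading too, the margin depends on inputs that the article does not state.

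**The case against.** The strongest objection is that a reader might infer that 80% power is reached only if nobody drops out. The documents do not support that. The sample size paragraph fixes neither rho nor m nor the effect-size scale, and Steps 3 and 4 show combinations that hold 80% with 54 or even 48 completers. This stands, and it limits the point to the figure as stated. It does not remove it: the article claims 80% at 60 completers and declares no slack.

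A second tempting inference is that the article itself predicts loss, because it mentions poor tolerability of water restriction. Under Outcomes measures that remark concerns longer restriction and explains why 10 hours was chosen. It is not evidence of attrition in this trial, and every loss rate used here is an assumption.

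It can also be said that the authors concede that little data supports the sample size and call the trial preliminary. That lowers the stakes, but the concession does not mention loss and leaves the two counts unreconciled.

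Finally, a condensed article may leave an attrition allowance to the full protocol. Its absence alone would be no finding. The point rests on two printed counts that agree only at zero loss.

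**Conclusion.** The concern holds in this form: the power statement is tied to 60 completers, recruitment is set at 60, and the stated figure therefore contains no allowance for loss. If 80% at 60 completers is taken as given, assumed losses of 10% to 20% cost about 4 to 10 percentage points of power, or raise the detectable effect from 0.34 to between about 0.36 and 0.38. That is a modest overstatement, and a trivial one if only one or two patients are lost.

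The size rests on the assumed loss and on the unstated correlation and number of measurements. It does not show that the trial will have less than 80% power for its planned comparison, since that cannot be determined from the article.

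**What to change.** In Sample size justification, say that 60 is the number randomised. State the assumed loss to 12 weeks and the resulting number of completers, and restate the power or detectable effect at that number. Do this for the planned 12-week baseline-adjusted comparison, and give the effect-size scale and the correlation used. If the inputs behind the 0.34 did contain slack, stating them will show it. Then use the same meaning of 60 in the abstract, Study design and study sample, and Overview of study procedures.

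This is a change of text. No added enrolment is needed, and the only cost is a slightly less favourable stated figure.

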## Discussion

This paper described the methodology of a clinical trial to assess the effectiveness of atorvastatin in treating NDI in lithium users. If atorvastatin is ultimately found to be effective for NDI, some of the risk associated to CKD, hypernatremia and AKI attributable to lithium could be attenuated, allowing a greater number of persons to use lithium more safely. Minimizing these risks of kidney disease associated with lithium use is important because it could potentially prevent acute and chronic medical health care services related to renal disease and psychiatric illness, possibly saving significant personal and health care costs worldwide.

The present study is the first RCT of atorvastatin in the treatment of Li-induced NDI. This study represents an advance in methodological rigor compared to previous studies examining the treatment of NDI [17]. These studies were similar in design to the present study, however these used very small sample sizes (*n* = 9, *n* = 11) [18, 25]. Hydrochlorothiazide (HCTZ), other diuretics, non-steroidal anti-inflammatory drugs (NSAIDs), and aspirin (ASA) have also been tried in NDI, but the studies supporting their use are almost exclusively from small uncontrolled trials/chart reviews [17]. In addition, there are limitations to the use of amiloride, diuretics, NSAIDs and other medications previously tested to treat NDI: these medications can lead to elevations in lithium levels contributing to increased risk of lithium-associated CNS and acute renal toxicity. We present an RCT with comparatively large sample size (*n* = 60), which will provide preliminary data to guide larger-scale international collaborative study.

### Limitations

There are some limitations to this proposed study. For our primary outcome, urine osmolality, we used a threshold of < 600 mOsm/Kg after 10 h of water restriction to define NDI and allow patients to enter the study. NDI is ideally more conservatively measured with an even lower urine osmolality threshold that is more specific/sensitive for NDI. However, a urine osmolality < 600 mOsm/Kg is a clinically prevalent entity (50% of patients), associated with poor renal outcomes and is nonetheless of clinical importance and utility [15]. Other trials have used similar thresholds (e.g. < 700 mOsm/kg) under similar 8–10-h water restriction periods, has been termed as “partial NDI” [25]. The overnight water restriction urine osmolality has relatively high sensitivity/specificity for NDI compared to the gold-stander 24-h urine collection, particularly in combination with self-reported fluid intake, which we are also measuring [31]. In addition, we plan to complete a sub-group analysis of patients with a urine osmolality < 300 mOsm/Kg.

## Conclusion

To our knowledge, this is the first planned RCT for the treatment of NDI using atorvastatin. Future trials could 1) further assess the effectiveness of atorvastatin in treating lithium-induced NDI in a larger sample and 2) examine atorvastatin in the prevention of lithium-induced NDI and CKD. If found effective, atorvastatin could ultimately be combined with lithium regimens to treat/prevent NDI, which in turn could reduce the risk of CKD and other renal adverse events in lithium users. This could potentially allow clinicians to prescribe lithium to a larger number of patients with bipolar disorder, depression and other psychiatric/neurological disorders: Both maximizing positive potential therapeutic benefits of lithium, while minimizing renal adverse events.

## Abbreviations

AKI: Acute Kidney Injury
ALT: Alanine Aminotransferase Test
ANOVA: Analysis of Variance
AQP2: Aquaporin 2
ASA: Aspirin
ASRMS: Altman Self-Rating Mania Scale
AST: Aspartate Aminotransferase Test
BMI: Body Mass Index
CKD: Chronic Kidney Disease
eGFR: Estimated Glumerular Filtration Rate
HCTZ: Hydrochlorothiazide
IRB: Institutional Review Board
LDL: Low Density Lipoprotein
MADRS: Montgomery Asberg Depression Rating Scale
NDI: Nephrogenic Diabetes Insipidus
NSAIDs: Non-Steriodal Anti-Inflammatory Drugs
QIDS: Quick Inventory of Depressive Symptoms
RCT: Randomized Controlled Trial
SCIP: Screen for Cognitive Impairment in Psychiatry
UOsm: Urinary Osmolality
YMRS: Young Mania Rating Scale
